## Abstract

**Background:**

Individuals living with cancer must learn to face not only the physical symptoms of their condition, but also the anxiety and uncertainty related to the progression of the disease, the anticipation of physical and emotional pain related to illness and treatment, the significant changes implied in living with cancer, as well as the fear of recurrence after remission. Mindfulness-based meditation constitutes a promising option to alleviate these manifestations.

**Methods/Design:**

This article presents the rationale and protocol development for a research project aimed at evaluating the effects of a mindfulness-based meditation intervention on quality of life, sleep, and mood in adolescents with cancer compared to a control group. A prospective, longitudinal, experimental design involving three time points (baseline, post-intervention, and follow-up) and two groups (experimental and control) was developed for this project. Participants will be assigned randomly to either group. Eligible participants are adolescents aged 11 to 18 years with a diagnosis of cancer, with no specific selection/exclusion based on type, stage, or trajectory of cancer. A final sample size of 28 participants is targeted. Adolescents in the experimental group will be completing the mindfulness meditation intervention, taught by two trained therapists. The intervention will comprise of eight weekly sessions, lasting 90 min each. Once the follow-up assessment is completed by the experimental group, wait-list controls will be offered to complete the mindfulness-based program. Intra-group analyses will serve to evaluate the impact of the mindfulness-based meditation intervention on quality of life, sleep, and mood pre-post intervention, as well as follow-up. Analyses will also be used to carry out inter-group comparisons between the experimental group and the wait-list controls. Voluntary participation, risk of attrition, and the small sample size are potential limitations of this project. In spite of possible limitations, this project will be one among very few aimed at improving quality of life, sleep, and mood in adolescents living with cancer, will evaluate the potential benefits of such a practice on both psychological and physical health of youth with cancer, and help in creating mindfulness-based intervention programs, in order to provide the necessary psychological help to adolescents living with cancer.

**Trial registration:**

Trial registration number:
NCT01783418

## Background

News of a cancer diagnosis has been said to induce the greatest psychological distress among all prognoses and illnesses
[1]. Thus, it often elicits a strong emotional reaction in teenagers and their parents
[2]. Individuals living with cancer must learn to face not only the physical symptoms of their condition, but also the anxiety and uncertainty related to the progression of the disease, the anticipation of physical and emotional pain related to illness and treatment, the significant changes implied in living with cancer (for example, hair loss, frequent visits to the hospital), as well as the fear of recurrence after remission
[3,4]. To address these challenges, various psychosocial approaches have been developed, including mind-body therapies. Mindfulness-based meditation, initially developed to improve quality of life in patients suffering from chronic illnesses, constitutes a promising option
[5]. The goal of this article is to describe the development, rationale, and first phase of a pilot study evaluating the effects of a mindfulness-based intervention on quality of life, mood, and sleep for teenagers with cancer.

### The mindfulness-based stress reduction program

Mindfulness can be defined as the process by which we ‘[…examine] who we are, with questioning our view of the world and our place in it, and […cultivate] some appreciation for the fullness of each moment we are alive. Most of all, it has to do with being in touch.’
[6]. It lies at the center of the Minfulness-Based Stress Reduction program (MBSR) developed by Kabat-Zinn and colleagues
[5]. Specifically, mindfulness meditation allows us to ‘[…pay] attention in a particular way: on purpose, in the present moment, and nonjudgmentally’.

Kabat-Zinn and colleagues
[5] initially developed the MBSR program to address, explore, and decrease emotional and physical pain in patients suffering from a chronic illness, while observing the connection between the mind and the body. Anxiety and worry fueled by past and future events are hypothesized to ruin both physical and psychological health by increasing levels of stress. Thus, the MBSR program aims to bring focus to the present moment
[7]. Its main goal is to bring awareness to different manifestations of stress, in order to detect first signs of anxiety and to act voluntarily and willingly to correct usual patterns of response. Thus, the anxiety and depression that often accompany stress can be targeted quickly, in order to achieve general wellbeing and peace of mind
[8].

### Literature review and rationale

As previously mentioned, individuals living with cancer are at risk for significant psychological distress
[3,4,9]. Approximately 20% to 30% of individuals with cancer manifest depressive symptoms of clinical significance
[10]. Moreover, chronic physical symptoms, such as sleep disorders and fatigue, tend to appear consequently to cancer treatments; approximately 85% of individuals with cancer suffer from sleep disorders
[11,12].

Recent studies have shown a positive impact of MBSR on psychological health in individuals with cancer. Specifically, a recent meta-analysis has indicated moderate effect sizes of mindfulness meditation on stress, anxiety, depression, quality of life, sleep, and fatigue related to cancer, highlighting the predominant role this practice can play in the individual’s psycho-social adaptation
[9]. Research has also shown both immediate and 1-year post-intervention positive impacts of the practice on stress, quality of life, and mood in the same population
[11,13,14]. Furthermore, the group setting in which MBSR takes place has been shown to decrease isolation and loneliness often observed in the context of cancer, therefore promoting better relationships and stronger social support, which, in turn, may explain improvements in mood and quality of life
[15].

Altogether, authors have concluded that mindfulness meditation has beneficial effects on physical and psychological symptoms among adults with different chronic illnesses, and could hence be a key tool in the treatment of these conditions
[16,17]. Emerging research in pediatrics is suggesting similar effects in children and adolescents
[18-21]. The few studies that have examined its effects on youth with chronic illnesses tend to suggest that mindfulness meditation acts similarly by decreasing physical and emotional pain
[22].

### Primary aim

This article presents the rationale and protocol development for a research project aimed at evaluating the effects of a mindfulness-based meditation intervention on quality of life, sleep, and mood in adolescents with cancer compared to a control group. In light of data available on adult populations and emerging from research in youth, three hypotheses are formulated: (1) mindfulness meditation will have beneficial effects on the mood of adolescents completing this practice; (2) mindfulness meditation will have beneficial effects on quality of life of the participants; and (3) mindfulness meditation will have beneficial effects on sleep quality of the participants.

Specifically, significant improvements are expected to be observed in quality of life, mood, and sleep between pre-intervention and post-intervention measures in the experimental group. These effects should be sustained 6-months post-intervention.

## Methods/Design

### Design overview

A prospective, longitudinal, experimental design involving three time points (baseline, post-intervention, and follow-up) and two groups (experimental and control) was developed for this project. Participants will be assigned randomly to either the experimental or control group. The longitudinal design will allow the evaluation of the short- and long-term effects of the intervention. Figure 
1 illustrates the overall design and subject flow for this project. All study procedures and consent forms received approval from both the Université de Montréal (certificate number CERFAS-2012-13-007-D) and Sainte-Justine Mother and Child University Hospital Center (file number 3550) ethics and scientific committees.

**Figure 1 F1:**
[figure not shown]
Design and subject flow.

### Participants

Based on prior studies testing cognitive-behavioral interventions in adolescents with cancer, eligible participants are adolescents aged 11 to 18 years with a diagnosis of cancer
[23-25]. In keeping with previous research, there will be no specific selection/exclusion based on type, stage, or trajectory of cancer
[11,26-28]. The intervention will be conducted in French. Therefore, participants are required to speak and understand the language. They must be willing to participate in an 8-week mindfulness meditation program and be available to complete the measures 6 months after the intervention. They must not have a diagnosis of severe mental illness.

Based on prior mindfulness intervention studies with adolescent populations and on usual number of participants in a mindfulness-intervention training group (as indicated by Kabat-Zinn and colleagues
[29] in the MBSR program) a final sample size of 28 participants is targeted
[13,29-33]. Taking into consideration attrition rates from prior research (20-30%), an additional 12 participants will be recruited
[2,34-36]. Thus, a total of 40 participants will be recruited. Participants will be randomly assigned to the experimental or control group, and immediately given a participant ID for confidentiality and anonymization purposes. Twenty adolescents will be completing the mindfulness meditation intervention, which will be taught by two trained therapists (doctoral clinical psychology student and psychiatrist). The intervention will comprise of eight weekly sessions, lasting 90 min each.

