### Randomization

Participants will be assigned to one of two groups according to a computer-generated randomization list (computerized random numbers). As such, participants will be randomly assigned with a 1:1 allocation ratio following permuted block design procedures, using block sizes of four. No stratification criteria will be used. The allocation sequence will be generated by an independent researcher not involved in this project after baseline measures, thus ensuring that therapists and recruiters are kept blind to the allocation of each participant. The allocation sequence will be password protected and only accessible by the independent researcher. The research assistant responsible for the logistics of this project - who is not part of the treatment team - will not be kept blind for allocation and will be responsible for contacting participants randomly assigned to the experimental condition.

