### Planned statistical analyses

Descriptive statistics on participant characteristics will be presented for each group at baseline. Means and standard deviations on primary and secondary outcome variables will be presented for each group at 8 weeks and 6 months.

The cut-point to reject the null hypothesis will be set at 5% (α ≤0.05). Primary hypotheses will first be tested using three mixed analyses of covariance (ANCOVA) with Bonferonni corrections and individual critical alpha levels at 1.67% (α ≤0.0167), that will allow comparison of data at each time-point
[54]. The use of mixed ANCOVAs will help reduce within-group error variance, namely by controlling for baseline differences between participants in each condition and by taking into account possible confounds (for example, age, diagnosis, cancer stage), while providing a higher statistical power in detecting an intervention effect (
[55,56]).These intra-group analyses will serve to evaluate the impact of the mindfulness-based meditation intervention on quality of life, sleep, and mood pre-post intervention, as well as follow-up.

Specifically, changes in quality of life scores (as indicated by the Pediatric Cancer Quality of Life Inventory) between baseline, 8 weeks and 6 months will be tested. Similarly, a change in sleep quality scores (as indicated by the Pittsburgh Sleep Quality Index) and mood scores (as indicated by the Depression and anxiety scales of the Beck Youth Inventories and the PANAS-C) will be tested between baseline, 8 weeks and 6 months. These analyses will also serve to test secondary hypotheses, by allowing inter-group comparisons between the experimental group and the wait-list controls. Specifically, a difference in quality of life scores, sleep quality scores, and mood scores at baseline, 8 weeks, and 6 months will be assessed between groups.

Comparable analyses will be conducted on the data collected from the second experimental group once participants from the wait list condition go through the intervention. All statistical analyses will be conducted using SPSS version 20 (SPSS Inc., Chicago, IL, USA).

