## Discussion

Voluntary participation to this project constitutes a potential limitation, as it could imply that adolescents and their parents who take part are individuals who are either: (1) genuinely interested in the concept of mindfulness and in the action of meditating, thus potentially displaying a higher level of mindfulness than the general population of adolescents with cancer; or (2) potentially healthier and in better shape than those who chose not to participate, as meditation can be demanding. In both cases, these potential confounds will likely limit our ability to generalize our results primarily to adolescents with cancer showing similar motivation and level of health.

We do expect recruitment challenges, specifically in terms of presenting our research to ill adolescents and their parents, convincing them to take part in this project, and the fact that pediatric cancers are less frequent than adult cancers. However, we will maximize recruitment by using multiple recruitment strategies and different avenues to publicize this study.

The risk for attrition is an additional limitation of this project. Given the target population for the study, it is possible that attrition will be observed during the process due to diverse reasons, namely deterioration of health, initiation, or reinitiation of treatment rounds. Drop-outs could also occur due to the challenging nature of the intervention. Participants may conclude that the program is not what they expected or is simply too demanding for them. Further drop-outs may occur 6 months post-intervention, as some participants may be lost to follow-up (for example, harder to reach, no longer motivated to participate in the project). In addition, the research team is weighing out different options to minimize attrition in the wait-list control group - namely, monetary compensation and/or additional iTunes gift cards.

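### As classically run, the named mixed ANCOVA drops anyone missing a visit (about 8 to 12 of 40), discarding week-8 scores already in hand; a likelihood-based mixed model would keep them

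*Protocol article*

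**What the plan says.** **Sample size (Protocol article, Participants).** The article states that "a final sample size of 28 participants is targeted", citing prior studies and the usual size of a training group. It continues: "Taking into consideration attrition rates from prior research (20-30%), an additional 12 participants will be recruited", so that "a total of 40 participants will be recruited". Under Randomization, participants are "randomly assigned with a 1:1 allocation ratio following permuted block design procedures, using block sizes of four", which gives 20 per arm.

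**Analysis (Planned statistical analyses; Statistical power).** "Primary hypotheses will first be tested using three mixed analyses of covariance (ANCOVA"), Bonferroni-corrected to 0.0167 each, covering quality of life, sleep and mood at baseline, 8 weeks and 6 months. The effect size attached to the pre-post analysis is partial eta squared. The software is SPSS version 20; no procedure within it is named.

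**Timing (Assessment time-points).** The second assessment falls at the end of the eighth session, with time set aside on site. The third, at 6 months, is sent by mail.

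**Dropout (Discussion).** Attrition is thought possible "due to diverse reasons, namely deterioration of health, initiation, or reinitiation of treatment rounds". Also: "Drop-outs could also occur due to the challenging nature of the intervention". Further loss may occur at 6 months. The team is weighing "different options to minimize attrition in the wait-list control group", such as payment or extra gift cards. The gift card already planned goes to every participant.

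**The concern.** A classical between-within ANCOVA over three visits needs a complete row for each participant. One missing visit removes the whole row, including visits that were attended. The design makes this likely: the last assessment is a mailed package six months after the programme ends, so a participant can have a week-8 score and no 6-month score. That week-8 score would then not count.

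Two things are at stake. The first is precision, in a trial of 40 that expects small effects. The second is bias. If experimental-arm participants who are doing worse leave more often, those who remain flatter the intervention. Until the wait-list arm is offered the programme, only the experimental arm is exposed to its demands, so this cause of dropout can act on one side only. The Pilot study endpoints section uses the effect sizes as indications of benefit and to judge which outcomes belong in a larger trial, so any inflation would carry forward.

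**Working it through.** **1. The plan's own figure.** Inputs: 28 remaining and 20–30% attrition (Participants).
- N = 28 / (1 − d). At d = 0.30: 28 / 0.70 = 40. At d = 0.20: 28 / 0.80 = 35.
- The stated 40 is therefore reproduced at the upper end of the range.

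**2. How many a complete-row analysis loses.**
- At 20%: 40 × 0.20 = 8 lost, 32 kept.
- At 30%: 40 × 0.30 = 12 lost, 28 kept.

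**3. Precision at week 8 if all loss comes after week 8 and is unrelated to outcome.** The article gives no SD or correlation between visits. Assume SD 1 and a correlation with baseline of r = 0.6, so the residual SD is √(1 − 0.36) = 0.8.
- All 20 per arm: 0.8 × √(2/20) = 0.253.
- Completers, 14 per arm: 0.8 × √(2/14) = 0.302.
- Ratio √(20/14) = 1.195, about 20% wider.
- Simulated trials, which also let the number of completers vary, give 0.257 and 0.315. No bias arises in this case.

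**4. Bias at week 8 when dropout depends on outcome.** Assumptions: 20 per arm, r = 0.6, true effect 0.30 SD, 30% dropout. Dropout in the experimental arm depends on the week-8 score (log-odds slope per SD, worse scores leaving more); dropout in the control arm is unrelated to outcome unless stated.

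| Setting | Completers | All available week-8 data |
|---|---|---|
| Slope 0.25, all dropout after week 8 | 0.35 | 0.30 |
| Slope 0.5, all after week 8 | 0.39 | 0.30 |
| Slope 1, all after week 8 | 0.46–0.48 | 0.30 |
| Slope 1, half before week 8 | 0.47 | 0.37–0.38 |
| Slope 1, all before week 8 | 0.47 | 0.47 |
| Slope 1 in both arms, all after week 8 | 0.30 | 0.30 |

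Ranges show the spread between separate simulation runs.

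**5. The same mechanism with no true effect** (slope 0.5–1.0 in the experimental arm only, r = 0.5–0.7, dropout after week 8). Complete-row ANCOVA shows a spurious benefit of 0.07–0.19 SD at week 8 and 0.03–0.07 SD at 6 months. Using all observed data under missing at random gives about 0 at both times.

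**The case against.** The strongest objection is that the article nowhere says it analyses completers only. A reader might infer this from the sample-size paragraph, but there 28 is a target after attrition, justified by earlier studies and group size. It is not defined as the analysis set or as those with all three assessments. No SPSS procedure is named, SPSS 20 can also fit likelihood-based models, and imputation is not excluded. The analysis population and missing-data rule may stand in a fuller document that is not shown, so their absence is not a fault. All of this stands. What remains is narrower: the article does name its primary model and a matching effect size, and the ordinary way of running that model deletes incomplete rows.

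A reader might also infer that missing data are bound to be informative and unequal by arm. The Discussion says only that such dropout is possible, could or may occur. Worsening health could act alike in both arms, and then the simulation shows no bias.

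Third, the gain from a better model depends on timing. Participants who find the programme too demanding may well leave before the eighth session, and the model recovers nothing for them. This also stands; it limits the benefit and is the reason for a sensitivity analysis.

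Finally, this is a pilot that openly lists attrition as a limitation, and the extra wait-list incentive is only under consideration. That makes the incentive a secondary matter. It does not justify losing scores already collected.

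**Conclusion.** The point holds in a limited form. The named model, as classically run, would remove about 8 to 12 of 40 participants at the stated attrition, and with them the week-8 scores of those lost only at 6 months. The article itself anticipates dropout that could be related to health and to the programme.

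The size is conditional. With dropout after week 8, a completer analysis costs about 20% in standard error (about 0.31 against 0.26). If that dropout is also related to outcome in the experimental arm only, with slope 0.5–1, it inflates a true 0.30 SD to 0.39–0.48. The advantage of using all data falls to nothing as dropout moves before week 8, and there is no bias if the mechanism is the same in both arms. These figures rest on an assumed SD, correlation, effect and dropout slope, none of which the article gives.

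The documents do not support saying that the plan restricts itself to completers, or that bias is certain. They do support changing the model, since the alternative is better or no worse in each setting examined.

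**What to change.** - Replace the mixed ANCOVA with a likelihood-based linear mixed model (SPSS MIXED, REML) for each outcome: 8-week and 6-month scores as outcomes, baseline score as covariate, group, time and group by time, and unstructured covariance.
- Include every randomised participant with at least one follow-up score, in the arm assigned.
- Add a sensitivity analysis that lets data be missing not at random, because the model assumes missing at random and does not recover those who leave before week 8.
- Secondary: if the extra retention incentive being weighed for the wait-list arm is adopted, offer it to both arms.

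Cost: the data and software stay the same. The model needs a few more lines of syntax and the sensitivity analysis a short addition to the plan. Any added incentive costs what it takes to extend it to the experimental arm.

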### Recruitment

Recruitment for this project has started in September 2012, and is performed in the oncology center of a university-affiliated pediatric hospital in a large urban area. Physicians and nurses have been invited to discuss the project with their patients when they visit the hospital for their regularly scheduled appointments. In addition, research nurses have screened hospital records to identify patients who qualify for this study (that is, teenagers with cancer and no ongoing or lifetime severe psychopathology, such as schizophrenia, psychosis, delusional disorders, or organic mental disorders), and introduced to them the project. Posters and brochures have been posted and available throughout the oncology wing of the hospital. Supplemental advertisement has been sent through the province-wide Association for Children with Cancer’s monthly newsletter, via mass emailing.

